An additional objective is to identify outcome predictors, including therapist and patients’ variables and the therapeutic relationship.*Hypothesis 4:**The following variables are expected to predict positive treatment outcomes:**Therapist variables: competencies, adherence, and allegiance; therapist-rated therapeutic relationship**Patient variables: preferred learning style at pre-treatment, changes in insights in SAD-related beliefs, changes in SAD-related cognitions; patient-rated therapeutic relationship.*

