### Study Procedures

All subjects contacted for the study will be screened over the telephone by trained master’s level research assistants. Those who seem eligible will be invited for two in-person assessments. The screening visit will include a diagnostic interview for Axis I and II disorders (SCID-I and SCID-II) and a semi-structured interview to assess the subject’s SAD and depression symptoms and insight into SAD-related beliefs (LSAS, SPIN, QIDS, BAPS). The diagnostic interviews will be conducted by trained [doctoral-level] independent raters who are blind to treatment conditions. Patients who are eligible will be randomized either to the CT plus enhanced BEs group or to the Standard CT group and invited for a baseline visit to complete a self-reported questionnaire. The outcome measures will be assessed by the independent raters upon the termination of treatment and after 6months. The study protocol adheres to the Standard Protocol Items: Recommendations for Interventional Trials (SPIRIT) checklist (Additional file 1).

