### Additional Assessments

For competence and adherence ratings, three videotapes will be selected: one from the initial stage (session 1, deriving the model) and two from the second stage (random selection from session 5–12). Session 1 is selected to cover general competencies such as guided discovery, whereas sessions from the second stage of treatment onwards are expected to refer to specific competencies (conducting BEs vs. cognitive restructuring). Competence and adherence will be rated by two independent, masked, and trained raters using the Cognitive Therapy Adherence Scale for Social Phobia (CTAS-SP) [18] the Cognitive Therapy Competence Scale for Social Phobia (CTCS-SP) [30]. The CTAS-SP comprises 17 items related to the specific interventions of CT, as described in the manual by Stangier et al. [17]. In the SOPHONET trial [6], a good interrater reliability (ICC = 0.87) was observed. Retest reliability was rtt = 0.90 for the total score and rtt = 0.28–1.0 for the individual items. Internal consistency was high (α = 0.99). Similarly, the psychometric properties of the 16-item CTCS-SP were good, with an interrater reliability of ICC = 0.81, retest reliability of rtt = 0.92, and an internal consistency of α = 0.97.

To assess the therapeutic relationship, the Helping Alliance Questionnaire (HAQ, patient and therapist version) will be used [31]. Both questionnaires will be administered at pre-treatment. The mean scores of the therapist and patient versions will be used to predict the outcomes.

Allegiance is assessed after the training and one pilot-therapy by the therapist version of the Reaction to Treatment Questionnaire developed by Holt & Heimberg [32]. For the purpose of the present study, two further items have been added to the scale referring to outcome expectations about specific intervention (BEs and cognitive restructuring).

As a predictor of treatment success, a 12-item version of the learning style inventory (Kolb LSI) will be administered at pre-treatment [33]. Based on previous treatment study results [34], it is hypothesized that the outcome of participants in the BE intervention will significantly predict an active experimentation learning style, whereas for participants in the standard CT (cognitive restructuring), the preferred learning style is predicted to be an abstract conceptualization learning style.

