The SCQ (Social Cognition Questionnaire) [35] (German translation [36]) is a self-report measure to assess the frequency and intensity of SAD-related cognitions. The questionnaire will be completed by the patients at every session.

Detailed procedure of the measurements is listed in the schedule of enrolment, interventions and assessments (Fig. 2).

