### Statistical Analyses

Data will be analyzed with the SPSS statistical software package. All statistical analyses will be conducted on the intent-to-treat (ITT) sample and completer sample. Patients allocated to treatments will be classified as drop-outs if they miss more than 25% of the sessions. In the ITT analyses of treatment response, drop-outs will be considered as failures. In ITT analyses of dimensional measures, missing data will be replaced using the last observation carried forward approach for missing intervention- and post-assessments or follow-up observations. Analyses of the primary outcome measure (CGI-I), a categorical variable, will be conducted using χ^2^ or Fisher's exact tests. Dimensional measures will be submitted to analyses of covariance (ANCOVAs) in which pre-treatment scores will be controlled for. ANCOVAS will be performed separately for the post-treatment and 6-month follow-up assessments. Significance levels will be set at *p* < 0.05, two-tailed. Predictor analysis will be calculated by using logistic regression analysis with CGI-I as the dependent variable; independent variables are competencies, adherence, allegiance, and therapist-rated therapeutic relationships (therapist predictors), as well as patients’ preferred learning style at pre-treatment, changes in insight in SAD-related beliefs and cognitions, and patient-rated therapeutic relationships (patient predictors). Differences between treatments in the outcome predictions will be analyzed, with treatment interactions for each predictor. To test for possible therapist differences, a preliminary analysis of covariance will be conducted. As recommended, significance level in this case will be set at *p* < .30 [37]. If the effect is significant, a multilevel analysis using a mixed-model design is planned to include therapists as a random term [38]. A final analysis will be run to compare the pattern of results from both strategies of analysis taking possible therapist effects into consideration.

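### The therapeutic-relationship questionnaire is given before therapy starts, so two Hypothesis 4 predictors cannot measure what they name; insight change is concurrent with post-treatment response

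*Protocol article*

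**What the plan says.** All places are in the protocol article.

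- **Additional Assessments** introduces the HAQ, in patient and therapist versions, as the measure of the therapeutic relationship. On timing: "Both questionnaires will be administered at pre-treatment". On use: "The mean scores of the therapist and patient versions will be used to predict the outcomes". The text gives no later administration.
- **Hypotheses** lists the patient predictors of Hypothesis 4 as "preferred learning style at pre-treatment, changes in insights in SAD-related beliefs, changes in SAD-related cognitions; patient-rated therapeutic relationship". The therapist predictors are competencies, adherence, allegiance and the therapist-rated relationship.
- **Statistical Analyses** plans a logistic regression with CGI-I as the dependent variable. Its patient predictors again include "changes in insight in SAD-related beliefs and cognitions, and patient-rated therapeutic relationships (patient predictors").
- **Outcome Measures** places CGI-I at post-treatment and 6-month follow-up. BABS is taken at pre-treatment, post-treatment and 6 months.
- **Additional Assessments** says of the SCQ: "The questionnaire will be completed by the patients at every session".

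**The concern.** A predictor must measure the named construct and must be observed before the outcome it is meant to predict. The HAQ fails the first condition, because it is completed before patient and therapist have worked together. A null result for alliance could then come from the timing alone, and a positive result would more naturally be read as an effect of expectation. Alliance that is not measured during therapy cannot be recovered afterwards.

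Insight change can fail the second condition. CGI-I is itself a rating of change from baseline. If BABS change over the same interval is set against CGI-I at the same visit, two descriptions of the same improvement are being correlated. A finding that insight change predicts response would then say little about what drives response.

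**Working it through.** No figure in the protocol is at issue. The check compares the time of each predictor with the time of the outcome.

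**Step 1. Count the predictors.** Statistical Analyses names four therapist and four patient predictors: 4 + 4 = 8.

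**Step 2. Compare the times.** CGI-I is rated at post-treatment and at 6 months.

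| Predictor | When measured (section) | Assessment |
|---|---|---|
| Patient-rated relationship (HAQ) | Pre-treatment (Additional Assessments) | Before any relationship exists |
| Therapist-rated relationship (HAQ) | Pre-treatment (same) | Before any relationship exists |
| Change in insight (BABS) | Pre, post, 6 months (Outcome Measures) | Only at visits where CGI data are taken |
| Change in cognitions (SCQ) | Every session (Additional Assessments) | Can precede the outcome; window open |
| Competence | Videotapes of session 1 and two of sessions 5–12 (same) | Precedes the outcome |
| Adherence | Same videotapes (same) | Precedes the outcome |
| Allegiance | After training and one pilot therapy (same) | Precedes the outcome |
| Learning style | Pre-treatment (same) | Precedes the outcome |

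The tally is 2 mistimed + 1 potentially concurrent + 1 open + 4 correctly ordered = 8.

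**Step 3. What pre-treatment means for the HAQ.** Under Study Procedures, eligible patients are randomised and then "invited for a baseline visit to complete a self-reported questionnaire". Under Randomization, the participant is allocated to a particular therapist. So at pre-treatment a therapist may have been assigned, but no session has been held. The therapist version would ask for a rating of a relationship with a patient not yet treated.

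**Step 4. Which BABS pairings are ordered.** Two change windows and two CGI-I times give four pairings:

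- baseline-to-post change, post-treatment CGI-I: concurrent;
- baseline-to-6-month change, 6-month CGI-I: concurrent;
- baseline-to-6-month change, post-treatment CGI-I: the predictor comes after the outcome;
- baseline-to-post change, 6-month CGI-I: the predictor comes first.

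Only one of the four supports the word prediction.

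**Step 5. How much concurrency could matter (illustration).** The documents give no correlation, so it is assumed and varied. A change score with no effect of its own was given a correlation *r* with the end-point state underlying CGI-I. Responders were set at 50% (assumed). A single-predictor logistic regression was fitted in 1,500 simulated data sets per setting.

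| *r* | p < 0.05, N = 54 | p < 0.05, N = 60 |
|---|---|---|
| 0 | 3.9% | 4.2% |
| 0.1 | 8.4% | 8.4% |
| 0.2 | 17.3% | 22.5% |
| 0.3 | 38.7% | 44.3% |
| 0.5 | 87.0% | 88.7% |

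A moderate shared end-point state is enough to make a score that drives nothing look like a predictor. The table shows the mechanism; it does not estimate the bias in this trial.

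**The case against.** **The schedule in Fig. 2 is not available.** It may list a later HAQ. That stands as a caveat, but the text names pre-treatment explicitly, so a later entry in the figure would be a discrepancy to reconcile.

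**A pre-treatment rating is not empty.** Patients are allocated to a therapist before the baseline visit, so an expectation of the relationship could be rated. This is true, but expectation is not the therapeutic relationship that Hypothesis 4 names.

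**The article fixes neither the change window nor the CGI-I time point, and such detail may sit in an analysis plan that is not shown.** This also stands, and it limits the second point. Concurrency is a consequence of one pairing for BABS, not something the protocol commits to. For SCQ no problem follows from the planned data.

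A reader might infer more than the text supports:

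- *That Hypothesis 4 cannot be answered at all.* Four of the eight predictors precede the outcome, and SCQ change can be scored so that it does.
- *That the same person scores BABS and CGI-I for a patient.* The protocol says only that raters are trained on both scales.
- *That one model carries every predictor and every interaction* (8 + 1 + 8 = 17 slopes). The text says "Differences between treatments in the outcome predictions will be analyzed, with treatment interactions for each predictor". It does not say that all enter jointly; one predictor at a time with its interaction fits the wording equally well.
- *That self-report after randomisation spoils the learning-style predictor.* That is a separate question about baselines, and nothing in the documents shows an effect on this inventory.

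**Conclusion.** The point holds for the HAQ: as written, two of eight Hypothesis 4 predictors do not measure the therapeutic relationship. This rests on the explicit timing in the text and on the unseen Fig. 2 not listing a later administration. It holds for BABS in a conditional form: baseline-to-post change against post-treatment CGI-I is association, and only baseline-to-post change against 6-month CGI-I is ordered in time. The size of any inflation cannot be derived from the documents.

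Competence, adherence, allegiance and learning style need no change in timing. Hypothesis 4 is an additional objective, so neither the primary responder comparison nor the secondary outcomes are affected. The change should still be made, because it is cheap and the missing alliance data cannot be collected later.

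**What to change.** 1. **HAQ.** Administer both versions at one fixed early session in both arms, for example after session 3, where Stage 1 ends in the CT plus BEs description, and use that score as the predictor. Standard CT is described as similar in Stage 1 but has more sessions in total (25 against 17), so state the point for each arm. If Fig. 2 already lists such an administration, correct the text to match.
2. **BABS.** Use baseline-to-post change to predict 6-month CGI-I response, preferably with post-treatment response in the model. Otherwise report it as a concurrent association.
3. **SCQ.** Use change from baseline to a fixed mid-treatment session, defined in advance for each arm. The text already has patients complete it at every session. Confirm that this applies in both arms, since the Treatments section describes weekly therapist use as a feature that standard CT lacks.
4. **Wording.** In Statistical Analyses, state the window of each change score and the CGI-I time point it is set against.

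The cost is one moved questionnaire and a few sentences. Patients already past the chosen session keep their pre-treatment HAQ and are flagged, and their scores should not be pooled with in-treatment ones. Patients who stop before that session will have no alliance score, which slightly reduces the sample for this predictor.

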### Hypotheses

The present study aims to investigate whether the enhanced implementation of BEs will improve the efficacy of CT for SAD. This goal will be achieved by the following measures:
comprehensive training of the therapists’ competencies in conducting in-session BEs, including self-practice and self-reflection,encouraging therapists to implement this intervention as the major component of the treatment in continuous supervision,establishing double hour sessions to ensure an appropriate setting for BEs.

The experimental condition (CT plus enhanced BEs) will be compared to standard CT as the control condition. An active control condition has been chosen as comparator to control for specific effects of conventional components of cognitive therapy. In standard CT, therapists’ training, supervision, and settings are arranged with a focus on traditional cognitive restructuring techniques.

In a randomized controlled trial, the following major hypothesis will be tested:*Hypothesis 1: As compared to standard CT, CT plus enhanced BEs will result in a significantly higher rate of responders at (a) post-treatment and (b) follow-up.*

The secondary objective is to identify differences in the process of therapy and their association with treatment outcomes. The process-related variables to be assessed include the following therapist variables: general and treatment-specific competencies, and adherence to and allegiance with the treatment manual. The patient variables and treatment outcomes are: changes in insight in SAD-related beliefs, cognitions, avoidance, and symptoms, as well as comorbid depressive symptoms.*Hypothesis 2: In the CT plus enhanced BEs, as compared to standard CT, therapists will show higher levels of adherence related to BEs, and significantly higher levels of allegiance with the treatment approach.**Hypothesis 3: In CT plus enhanced BEs, as compared to standard CT, changes in SAD-related insights, cognitions, avoidance, and symptoms (a) from baseline to post-treatment, and (b) from baseline to follow-up will be significantly increased.*

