### Randomization

We will use two levels of randomization. Firstly, therapists are randomized to either CT + BEs or Standard CT as described above. Secondly, participants will be randomly assigned to a therapist of one of the two treatment conditions. The random allocation sequence will be generated by a randomization program [19]. Allocation to treatment of the patients is concealed from investigators and patients. The random allocation schedule will be drawn up and administered by a psychologist from another department of the university who is not involved in the further study process. After meeting the inclusion criteria, the participant is allocated by this psychologist to a therapist of one of the treatment conditions. The investigators and therapists are informed about the allocation.

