**Data monitoring and quality assurance**

There will be no auditing process by an institution or agency independent from the investigators. The integrity of data quality is ensured by independent clinical raters assessing inclusion criteria and primary outcome. Random allocation to treatment will be administered by a psychologist from another department of the university. Adherence to trial interventions is ensured by checklists of interventions endorsed by therapists after each session, as well as videotapes of session. Supervision of therapists is provided separately by either the senior investigator for the experimental condition, or by an independent supervisor for the control condition. Allegiance of therapists in both study conditions is assessed after the pilot therapy. Completeness, accuracy, and timeliness of data collection is checked by the Co-investigators. Serious adverse events and harms are reported to the senior investigator, who will conduct interviews and refer the patient to crisis intervention in the center for psychotherapy affiliated to the department of psychology.

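### Allegiance is scored once per therapist but tested in a single-level patient logistic regression, so the hypothesis 4 test is anticonservative if therapists are few and residual therapist variance remains

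*Protocol article*

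**What the plan says.** **How allegiance is measured.** Under Additional Assessments: "Allegiance is assessed after the training and one pilot-therapy by the therapist version of the Reaction to Treatment Questionnaire". Under Data monitoring and quality assurance: "Allegiance of therapists in both study conditions is assessed after the pilot therapy". Neither place mentions a repeat for each trial patient.

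**How patients relate to therapists.** Under Randomization, "participants will be randomly assigned to a therapist of one of the two treatment conditions". Under Therapists, each therapist is allocated to one condition only. The number of therapists is not given.

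**How allegiance is tested.** Under Statistical Analyses: "Predictor analysis will be calculated by using logistic regression analysis with CGI-I as the dependent variable; independent variables are competencies, adherence, allegiance". The list goes on to patient-level predictors, and a treatment interaction is planned for each predictor. No therapist term is named for this model.

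**What is planned for therapist effects.** Later in the same section: "To test for possible therapist differences, a preliminary analysis of covariance will be conducted", with a threshold of p < .30. Then: "If the effect is significant, a multilevel analysis using a mixed-model design is planned", with therapists as a random term. A last analysis compares the results of the two strategies.

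**The concern.** A predictor that is constant within a therapist gets its information from contrasts between therapists. If patients of the same therapist tend to have similar outcomes for reasons other than allegiance, a model that treats the patients as independent overstates that information. The standard error is then too small and the Wald test rejects too often. Allegiance is the clear case here. Competence and adherence are rated from videotapes of each treatment, and the alliance questionnaire also has a patient version, so those predictors can vary between patients of one therapist.

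What is at stake is the claim in hypothesis 4 that allegiance predicts response. Hypothesis 4 presumes that therapist characteristics affect outcome, so zero therapist variance is an uncomfortable default in this trial. The therapist term that would protect the test depends on a preliminary test. That test is an analysis of covariance, the method the section names for dimensional measures, whereas the predictor model has a binary outcome.

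**Working it through.** The article states no figure for the allegiance test, so there is none to reproduce.

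**Inputs from the article.** 60 patients, 30 per group (Design and Sample Size); two-sided 5% tests and the p < .30 threshold (Statistical Analyses); one allegiance score per therapist.

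**Assumed, because not given.** K = 6 to 30 therapists with equal caseloads m = 60/K; ICC from 0 to 0.20 on the logit scale; 55% response.

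**Step 1: approximation.** For a predictor constant within therapist, the variance is inflated by DE = 1 + (m − 1) × ICC. The ratio of naive to true standard error is 1/√DE. The approximate type I error is 2 × [1 − Φ(1.96/√DE)]. Example with K = 10, m = 6, ICC 0.10: DE = 1 + 5 × 0.10 = 1.50; ratio = 1/√1.50 = 0.82; 1.96 × 0.816 = 1.60; type I error about 0.110.

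**Step 2: simulation.** Null data sets (6,000 per setting) were analysed with a single-level logistic model containing arm and allegiance.

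| Therapists (patients each) | ICC | DE | SE ratio | Approximate error | Simulated error |
|---|---|---|---|---|---|
| 6 (10) | 0.05 | 1.45 | 0.83 | 0.104 | 0.093 |
| 6 (10) | 0.10 | 1.90 | 0.73 | 0.155 | 0.134 |
| 10 (6) | 0.05 | 1.25 | 0.89 | 0.080 | 0.071 |
| 10 (6) | 0.10 | 1.50 | 0.82 | 0.110 | 0.094 |
| 20 (3) | 0.05 | 1.10 | 0.95 | 0.062 | 0.050 |
| 20 (3) | 0.10 | 1.20 | 0.91 | 0.074 | 0.061 |
| 30 (2) | 0.05 | 1.05 | 0.98 | 0.056 | 0.051 |
| 30 (2) | 0.10 | 1.10 | 0.95 | 0.062 | 0.051 |

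The Monte Carlo standard error near 5% is √(0.05 × 0.95/6000) = 0.003. At ICC 0 the simulated error is 0.042 to 0.050 for every K, so there is no inflation. At ICC 0.20 it is 0.206 (K = 6), 0.138 (K = 10), 0.079 (K = 20) and 0.065 (K = 30).

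**Step 3: the pre-test.** It was modelled as an F test for therapists within arm on a continuous score with the same ICC and the same therapist effects.

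| ICC | Pre-test below .30, K = 6 to 30 |
|---|---|
| 0.05 | 39-52% of trials |
| 0.10 | 51-67% |
| 0.20 | 72-85% |

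Suppose a significant pre-test leads to a therapist-level test of allegiance, and otherwise the single-level test stands. Overall type I error is then 0.048 to 0.073 for ICC 0.05 to 0.20. In the trials where the pre-test is not significant, the single-level test still has an error of about 0.05 to 0.14.

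**Step 4: the remedy.** A therapist-level regression of response proportions on arm and allegiance, with K − 3 degrees of freedom, gives 0.045 to 0.056 in every setting.

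**Limits.** The simulated model has arm and allegiance only. The planned model has more predictors plus treatment interactions, and these could change the residual therapist variance.

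**The case against.** The strongest reply is that the section already has a safeguard. The pre-test threshold is liberal, the random term it leads to is the standard way to handle a predictor shared within therapist, and a comparison of both strategies is promised. The pre-test is also significant most often where inflation is worst. This stands in part: if the safeguard covers the predictor model and leads to a valid therapist-level test, little inflation is left (at most 7.3% in these settings). But the article does not say that it covers this model, and when the pre-test is not significant the single-level result stands.

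A second reply is that the size rests on assumptions. That is correct. With 20 or 30 therapists and an ICC of 0.05 to 0.10 the inflation is negligible, and with no residual therapist variance there is none. A reader might infer that the standard error is always too small, or that the patients add no information at all. The documents support neither reading.

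A reader might also infer that hypothesis 2 will be tested with each therapist's score copied to every patient, which would inflate its error badly. Nothing in the article says so. Hypothesis 2 predicts that therapists in the experimental arm will show "significantly higher levels of allegiance with the treatment approach", and the quality assurance text speaks of allegiance of therapists. One score per therapist is the natural reading, so for hypothesis 2 this is only a clarification.

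Nor would an anticonservative test falsely clear allegiance as an explanation of a treatment difference. It would err towards declaring allegiance effects.

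**Conclusion.** The point holds in a limited form. As written, the hypothesis 4 test of allegiance uses a patient-level model for a therapist-level score. It is anticonservative if residual therapist variance remains, therapists are few, and the random-term step does not apply or is not triggered. Under the assumed ICCs of 0.05 to 0.10, type I error without that step is about 9-13% with 6 therapists, 7-9% with 10 and 5-6% with 20. With the step applied and leading to a valid test, it is about 5-7%. The number of therapists and the ICC are assumptions throughout, so these are ranges and not estimates for this trial.

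Hypothesis 4 is an additional objective. The primary comparison of CGI-I response between arms is not affected by this point. The change is still worth making, because the rule is stated, the correction is small, and it removes dependence on a pre-test whose scope is unclear.

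**What to change.** Under Statistical Analyses, state that allegiance, and any other predictor constant within therapist, is tested with therapist clustering allowed for whatever the p < .30 pre-test shows. Either of two forms will do:

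- a mixed logistic model with a therapist random intercept and small-sample degrees of freedom; or
- a therapist-level analysis, with degrees of freedom set by the number of therapists.

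With very few therapists the second is the safer choice, because the random-intercept variance may be estimated as zero and the mixed model then falls back to the single-level one. The allegiance-by-treatment interaction should be handled in the same way. A short clarification that hypothesis 2 compares one allegiance score per therapist would remove any doubt there.

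The change is to wording only; no extra data are needed. The cost is wider intervals for therapist-level effects. In the therapist-level form with K − 3 degrees of freedom, the 95% multiplier rises from 1.96 to about 3.18 with 6 therapists (3 df), 2.36 with 10 (7 df) and 2.11 with 20 (17 df). With few therapists the trial can say little about allegiance, and the wider interval shows that.
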